### Secondary outcomes

#### Cardiorespiratory fitness ($$ \dot{\mathrm{V}}{\mathrm{O}}_{2\mathrm{peak}} $$)

Cardiorespiratory fitness represents a strong predictor of decreased total cancer mortality risk, independent of adiposity [46, 47]. $$ \dot{\mathrm{V}}{\mathrm{O}}_{2\mathrm{peak}} $$ and exercise duration during the $$ \dot{\mathrm{V}}{\mathrm{O}}_{2\mathrm{peak}} $$ test will be used as measures of cardiorespiratory capacity. The $$ \dot{\mathrm{V}}{\mathrm{O}}_{2\mathrm{peak}} $$ test will be conducted as previously described by Devin et al. [48].

#### Body composition

High adipose tissue and reduced skeletal muscle has been associated with poorer short-term recovery following cancer treatment and poorer survival [49, 50]. Furthermore, a decline in bone mineral density, particularly trabecular density, has been correlated with increased fracture risk and subsequent decreased quality of life [51]. Regional and whole-body lean mass, fat mass and bone mineral density will be measured using dual energy x-ray absorptiometry (DXA, Hologic Discovery A, Waltham, MA) as previously described by Devin et al. [19] and Bolam et al. [52]. The coefficients of variation values in our laboratory are < 1.1%.

#### Anthropometry

Obesity, particularly around the abdomen, has been directly associated with risk of several types of cancer, including cancer of the breast and colon. In addition, both body mass index (BMI) and waist circumference have been separately associated with a decrease in global health status, functioning and symptoms of fatigue [53]. Therefore, prevention of weight gain is important for reducing the risk of cancer recurrence [54–56].

Height and body mass will be measured using a stadiometer (Seca, Birmingham, UK) and electronic scales (A & D Mercury, Pty Ltd., Thebarton, Aus.), respectively, from which BMI will be calculated. Waist and hip circumference will be measured using an anthropometric steel tape measure (Lufkin W606 M retractable steel tape; Cooper Tools), from which a waist-to-hip ratio will be determined. All anthropometrics will be measured according to the International Society for the Advancement of Kinathropometry (ISAK) procedures [57]. Measures will be recorded to the nearest 0.1 cm or 0.01 kg in duplicate, with mean values used in subsequent analyses. If duplicate measures vary by ≥2%, a third measure will be taken with the median value used in subsequent analyses.

#### Isometric grip strength

Cancer treatment commonly results in reduced muscle strength which leads to decreased functional capacity and potential declines in quality of life and survival [58, 59]. Dominant and non-dominant handgrip strength will be assessed using a spring-loaded grip dynamometer (TTM, Tokyo, Japan) to estimate physical performance and muscular strength [60]. Participants will perform a 3-s maximal contraction with each hand maintaining a 90^o^ elbow flexion and limit accessory movements [61]. Three trials will be performed on each side, alternating between the dominant and non-dominant hand with the best result used in subsequent analysis. A rest period of at least 30 s will be provided between subsequent attempts.

#### Blood biomarkers

Resting samples of venous blood (20 ml) will be drawn by a qualified and experienced phlebotomist. Plasma and serum samples will be separated according to standard procedures and stored in a − 80 °C freezer for subsequent batch testing. Plasma samples will be analysed for interleukin 6, interleukin 8, tumour necrosis factor – alpha and C-reactive protein, which have been identified as key mediators of neuro-immune interactions associated with post-treatment fatigue in cancer survivors [62, 63]. Additional analyses of insulin-like growth factor-1 (IGF-1), − 2 (IGF-2), and -binding protein-3 (IGFBP-3) will be explored as plausible mechanisms underpinning the inverse association between physical activity and cancer progression [64]. Plasma cytokines will be assessed using high-sensitivity ELISAs (R&D Systems, Minneapolis, MN) following the manufacturer’s specifications. Quality control procedures for the laboratory will be conducted in the manner reported by Aziz et al. [65]. All samples for a given participant will be run in parallel to minimise inter-assay variability.

#### Self-reported physical activity (Godin leisure-time physical activity questionnaire)

Leisure-time PA is a primary domain of intervention and research in public health [66]. Compared to other forms of physical activity (e.g. occupational), leisure-time PA may provide the greatest opportunity for enjoyment and improvement in cardiorespiratory fitness and health [67, 68]. The Godin Leisure-Time Physical Activity Questionnaire is a frequently used measure of leisure-time PA and will be completed at all testing time points [69]. The questionnaire requires participants to recall during a typical 7-day week the frequency and duration of exercise completed at three separate intensities: mild, moderate, and strenuous intensity. These values are used to calculate a weekly leisure-time activity index based on summing the frequency of sessions completed multiplied by a weighting factor for each level of intensity. The Godin questionnaire has been shown to have a modest correlation compared with accelerometry-derived measures of physical activity (r = 0.45) but demonstrates high test-retest reliability (r = 0.75) [70–72].

#### Sedentary behaviour and light physical activity

Sedentary behaviour (SB) is an independent risk factor for cancer incidence and mortality [73]. Comparably, moderate-to-vigorous intensity exercise generally delivers the greatest health benefits [74]. Exercise guidelines for people with cancer [22], however, acknowledge that any PA, including light physical activity (LPA), is better than none [73, 75]. Therefore, SB and LPA will be assessed using Actigraph GT3X+ accelerometry (Pensacola, Florida), following the methods described for MVPA. Time spent in SB will be calculated using Actilife v6 (Pensacola, Florida) and the cutpoints described by Matthews et al. [45] and time spent in LPA will be determined as the time spent above the SB cutpoint (≤ 100 counts per minute) and below the MVPA cut-point (≥ 2020 counts per minute) [44, 45].

#### Cancer-specific quality of life (EORTC QLQ-C30)

The European Organization for Research and Treatment of Cancer quality of life questionnaire for people with cancer is designed to assess quality of life in cancer patients and holds good internal consistency and clinical validity [76]. The EORTC QLQ-C30 [76–79] is a 30-item cancer-specific instrument including nine multi-item scales; five functional scales (physical, role, cognitive, emotional, and social); three symptom scales (fatigue, pain, and nausea and vomiting); and a global health and quality-of-life scale. The EORTC QLQ-C30 questionnaire has been shown as reliable and valid for use in cancer populations [78].

#### General health and wellbeing (SF-36)

The Medical Outcomes Study 36-item short-form 36 Health Survey (SF-36) will be used to assess general health and wellbeing domains of physical and mental health [80]. The SF-36 is scored through a set of eight scales encompassing physical and mental health measures. This survey has been shown to be reliable and has been validated for comparing general and specific populations, and estimating the relative burden of disease [81].

#### Health-related quality of life (FACT-G)

Quality of life will be measured using the Functional Assessment of Cancer Therapy-General (FACT-G) self-report questionnaire [82]. The FACT-G comprises four subscales: Physical Well-Being (PWB), Social/Family Well-Being (SWB), Emotional Well-Being (EWB), and Functional Well-Being (FWB). The FACT-G has been widely used in clinical trials, is relatively simple, and has demonstrated sensitivity according to the performance status and extent of disease [82, 83]. This questionnaire has been extensively used in oncology clinical trials, due to its ease of administration, brevity, reliability, validity, and responsiveness to clinical change [82]. The English language version of the FACT-G will be self-administered by participants.

#### Cancer-related fatigue (FACIT-F)

Fatigue will be assessed by the Functional Assessment of Chronic Illness Therapy Fatigue Subscale Questionnaire (FACIT-F) as described by Yellen et al. [84]. The FACIT-F is a 13-item fatigue subscale utilising a five-point Likert self-report scale ranging from 0 (not at all) to 4 (very much so). The total score varies from 0 (worst condition) to 52 (best condition) and is calculated as a sum of all items. The score is determined after re-parameterization of items 7 (I have energy) and 8 (I am able to do my usual activities) where 0 is worst condition and 4 is best condition, which have an inverse relationship to the other 11 subscale items. The FACIT-F questionnaire is reliable and has previously been validated for predicting efficacy in treatment outcomes in oncological-induced fatigue with high sensitivity (0.92) and reasonable specificity (0.69) [85]. Furthermore, convergent and discriminant validity testing has previously demonstrated a significant positive relationship with other measures of fatigue and a negative correlation with vigour [86].

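### The FACIT-F scoring rule recodes the two items that already run worst-to-best, so the total runs opposite to the stated 0 (worst) to 52 (best)

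*Protocol article*

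**What the plan says.** The scoring is given in the protocol article under Secondary outcomes, Cancer-related fatigue (FACIT-F). That section fixes four things.

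- Items and responses: "The FACIT-F is a 13-item fatigue subscale utilising a five-point Likert self-report scale ranging from 0 (not at all) to 4 (very much so".
- Total: "The total score varies from 0 (worst condition) to 52 (best condition) and is calculated as a sum of all items".
- Recoding: "The score is determined after re-parameterization of items 7 (I have energy) and 8 (I am able to do my usual activities".
- Direction of those two items: "where 0 is worst condition and 4 is best condition, which have an inverse relationship to the other 11 subscale items".

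The section mentions no recoding of the other 11 items, and no other part of the article gives a FACIT-F scoring rule. Table 1 lists FACIT-F as a secondary outcome at five assessments: before and after the supervised phase, and at 3, 6 and 12 months.

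**The concern.** A summed scale with a stated direction needs every item to point that way before summing. Items 7 and 8 ask about having energy and managing usual activities. With 4 meaning the strongest agreement, a 4 on either is a good state, so both already point towards the stated best end. The section itself says the other 11 run inversely to them. Those 11 are the items that need reversing, yet the text recodes the two.

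What is at stake is the sign of a secondary result. A total built by the printed rule and interpreted on the printed direction would turn less fatigue in the peer support group into an apparent worsening, and would turn a real worsening into an apparent benefit. The range checks described under Data collection, management and monitoring would not reveal it, because a reversed total still lies between 0 and 52.

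**Working it through.** **Inputs**, all from the FACIT-F section: 13 items, each scored 0 to 4; two items (7 and 8) for which 4 is the best state; 11 items running the opposite way, for which 4 is the worst state; total = sum of the items.

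Write X for the raw sum of the 11 items (0 to 44) and Y for the raw sum of items 7 and 8 (0 to 8). The worst possible respondent has X = 11 × 4 = 44 and Y = 0. The best has X = 0 and Y = 2 × 4 = 8. Reversing an item means replacing its response by 4 minus the response, so reversing the 11 gives 44 − X and reversing the two gives 8 − Y.

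**The plan's own figure.** The width reproduces: 13 × 4 = 52. The direction does not, as the four possible recodings show.

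| Recoding | Total | Worst state | Best state |
|---|---|---|---|
| Items 7 and 8 only (plain reading of the text) | X + (8 − Y) | 44 + 8 = 52 | 0 + 0 = 0 |
| No effective reversal | X + Y | 44 + 0 = 44 | 0 + 8 = 8 |
| The other 11 only | (44 − X) + Y | 0 + 0 = 0 | 44 + 8 = 52 |
| All 13 | (44 − X) + (8 − Y) | 0 + 8 = 8 | 44 + 0 = 44 |

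Only the third row gives 0 for the worst state and 52 for the best. Call that intended score I = 44 − X + Y.

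**Plain reading.** The total is X + 8 − Y = 52 − (44 − X + Y) = 52 − I. The reversal is exact for every respondent, so every between-group difference keeps its size and changes sign.

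**Alternative reading.** Suppose the clause about 0 being worst and 4 being best describes items 7 and 8 after recoding. They already run that way, so nothing effectively changes and the total is X + Y. Since X = 44 + Y − I, this equals 44 − I + 2Y. A between-group difference is then minus the intended difference plus twice the difference in Y. The end points still run the wrong way (44 worst, 8 best), but items 7 and 8 now partly cancel the other 11. The result is a mixed score, not a mirror image, and its sign does not have to flip in every case.

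**The validity sentence.** The section also reports a "significant positive relationship with other measures of fatigue and a negative correlation with vigour". That would fit a higher-is-worse total if the comparison measures score upwards, but the article does not give their direction, so it settles nothing.

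**The case against.** The strongest reply has four parts.

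1. The sentence can be read as describing items 7 and 8 after recoding, so the exact reversal is not the only thing it might prescribe. This stands: the 52-minus-score result belongs to the plain reading alone. It does not rescue the rule, because the alternative gives 44 (worst) to 8 (best), which still contradicts the stated range and direction.

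2. The intended scale is plain from the stated anchors, the section cites a source for the instrument, and an analyst could work back to the one recoding that fits. This is fair as an account of how the slip probably arose. But the source is not reproduced in the article, and an analyst has to notice the conflict before resolving it. The point is also not a detail left out by a condensed article: the article prints a rule, and the rule conflicts with the sentence just before it.

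3. Harm follows only if the scoring code obeys the literal sentence and nobody notices that respondents with little fatigue score near 0. This is correct. Nothing in the article shows how the code was written, so the consequence is conditional.

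4. The scope is small. FACIT-F is one of many secondary outcomes, the EORTC QLQ-C30 includes a fatigue scale whose results would disagree with a flipped FACIT-F, and stored responses can be rescored at any time. All of this stands. It limits the weight of the point without making the rule correct.

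**Conclusion.** The concern holds. No reading of the printed rule produces a total running from 0 (worst) to 52 (best). On the plain reading the total is exactly 52 minus the intended score, and the sign of every group difference on this scale flips. On the alternative reading the total runs from 44 (worst) to 8 (best) and mixes items pointing in opposite directions.

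The conclusion rests only on the response anchors, the content of items 7 and 8 and the section's own statement that they are inverse to the other 11. A misreported result further requires that the printed rule is what gets coded and that the output is read with 52 as best. The effect is confined to this secondary outcome; the primary MVPA analysis and the sample size are untouched. It should be corrected because it concerns the direction of a reported effect and costs almost nothing to put right.

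**What to change.** Replace the recoding sentence with a rule along these lines: reverse the 11 fatigue items (4 minus the response), score items 7 and 8 as answered, and sum all 13, giving 0 (worst) to 52 (best). Put the same rule in the scoring code and test it on two artificial respondents: 4 on the 11 items with 0 on items 7 and 8 must return 0, and the opposite pattern must return 52. It would also help to state the direction of the comparison measures in the validity sentence.

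The cost is one sentence and a check of the scoring code. No new data are needed, and any totals already computed can be rescored from the item responses.

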#### Insomnia (ISI)

The Insomnia Severity Index (ISI) is a seven-item measure of the nature, severity and impact of insomnia on a Likert scale (0 = *not at all*, to 4 = *very much*) [87]. Questions relate to the subjective qualities of the respondents’ sleep, including satisfaction with sleep patterns, the degree to which insomnia interferes with daily functioning, and how the respondent feels their insomnia is noticeable to others [88]. The ISI has shown internal validity (r = 0.76) in insomnia diagnosis [87], and reliability of α = 0.90 in breast and prostate cancer [89].

#### Psychological distress (BSI)

The Brief Symptom Inventory (BSI) [90] is a 53-item self-report symptom inventory that assesses nine patterns of clinically relevant psychological symptoms. It is a brief version of the Symptom Checklist List 90-R (SCL-90-R). Correlations between the BSI and SCL-R-90 are reported to range from 0.92 to 0.99 [90, 91]. Participants rate the extent to which they have been bothered (0 =“not at all” to 4 = “extremely”) in the past week by various symptoms [91]. The nine dimensions assessed are: somatization, obsession-compulsion, interpersonal sensitivity, depression, anxiety, hostility, phobic anxiety, paranoid ideation and psychoticism. The BSI also includes three indices of global distress: Global Severity Index, Positive Symptom Distress Index, and Positive Symptom Total. The BSI has been used in a variety of clinical and counselling settings as a mental health-screening tool and as a method of measuring symptom reduction during and after treatment. Research has previously found somatisation and anxiety to be related to physical activity levels in colorectal cancer survivors [92].

#### Depression, anxiety and stress scale (DASS)

The DASS questionnaire is a 42-item self-report instrument design to measure the three related negative emotional states of depression, anxiety, and stress [93]. Participants will be asked to plot their relative emotional feelings on a 0–3 scale (i.e. 0 being ‘did not apply to me at all’ and 3 being ‘applied to me very much, or most of the time) over each emotional domain [93]. The DASS has been clinically validated in measuring emotional states of depression, anxiety and stress in clinical populations and has good reliability and moderate sensitivity [94].

#### Depression and generalised anxiety (PHQ-9)

Depression is highly prevalent among people with cancer, with rates of depressive spectrum disorders as high as 58% [95]. The Patient Health Questionnaire-9 (PHQ-9) is a multipurpose instrument that will be used to assess severity of depression [96]. The diagnostic validity of the PHQ-9 was established in studies involving eight primary care and seven obstetrical clinics. PHQ scores ≥10 had a sensitivity of 88% and a specificity of 88% for major depression [96, 97]. PHQ-9 scores of 5, 10, 15, and 20 represents mild, moderate, moderately severe and severe depression [98].

#### Generalised anxiety disorder (GAD-7)

Approximately 20% of long-term cancer survivors report anxiety symptoms [99]. The GAD-7 is a self-administered patient questionnaire used as a screening tool and severity measure for generalised anxiety disorder [100]. GAD-7 has seven items, which measure severity of various signs of GAD according to reported response categories with assigned points [100].

#### Participant:peer supporter relationship

The quality of the bond between the peer-supporters and their participants will be assessed using an adapted version of the Working Alliance Inventory (WAI) questionnaire [101]. The WAI is a 7-point Likert-type measure that assesses 12 alliance dimensions including ‘agreement on task’, ‘agreement of goals’ and ‘development of bonds’, amongst others [102, 103]. The WAI has demonstrated high construct validity and high internal consistency estimates [103]. The WAI has been adapted for terminology relevance regarding ‘HIIT’ and ‘peers’ in this study. Furthermore, the 7-point Likert scale has been condensed to a 5-point Likert scale for consistency and ease of interpretation with the other study questionnaires.

#### Self-efficacy

To assess self-efficacy beliefs, participants will review the exercise recommendations for this trial (3 x HIIT sessions per week), and indicate the extent to which they feel capable of successfully adhering to these recommendations. Specifically, participants will be asked to what extent they would rate the truth of the statement ‘I feel capable of successfully completing 3 x HIIT sessions per week for 4 weeks, 3 months, 6 months, 9 months, and 12 months’, respectively. Participants will be asked to rate their responses on a 5-point Likert scale ranging from ‘strongly disagree’ to ‘strongly agree’. This method of assessing self-efficacy has been adapted from the Self-Efficacy for Exercise (SEE) scale which was originally described and validated in older adults by Resnick & Jenkins [104].

#### Barriers and enablers to exercise participation

Barriers and enablers to exercise participation will be assessed via two open-ended written questions about barriers and enablers to physical activity/exercise, as described by Evenson et al. and Macniven et al. [105, 106]. The barrier question will ask: ‘What is the one main reason that makes it harder for you to be more active?’. The enabler question will ask: ‘What is the one main reason that helps you to be more active?’. Two investigators will code responses and any discrepancies will be resolved by consensus. These items will be grouped into meaningful categories considering the socioecological framework, with intrapersonal, interpersonal, neighborhood or environmental, and organizational or policy categories.

Participants will also be asked to provide statements based on the Behavioural Regulation in Exercise Questionnaire Version 2, as previously used by Martin et al. and Markland et al. [24] [107]. Participants will be asked to respond to matrix-based questions such as ‘I find it difficult to exercise because of fatigue’ and ‘I am motivated to perform exercise because it will improve my physical health’. Participants will rate their agreement with the statements on a 5-point Likert scale ranging from ‘strongly disagree’ to ‘strongly agree’.

### Tertiary outcomes

#### Semi-structured interviews

At the end of each individual’s involvement in the study, participants and peer supporters will be invited to partake in a semi-structured interview (approximately 1 h) in-person or via telephone regarding their views and experiences throughout the trial. This will include study completers, as well as those who withdraw or fail to complete the study. Interview questions will focus on the participant’s experiences as a cancer survivor, with exercise and their participation in the trial. Peer supporters and participants who were randomised to receive peer support will be asked additional questions on their experiences providing and receiving peer support, respectively. Interviews will be audio-recorded and transcribed verbatim before undergoing inductive thematic analysis [108].

#### Physical activity preferences

The physical activity preference questionnaire will be used to assess the physical activity context preferred by participants throughout the duration of the trial due to its potential role as a covariate [109]. The questionnaire assesses physical activity preferences for 14 contexts of format (e.g. vigorous), location (e.g. outdoors), and social setting (e.g. done alone). Participants will be asked to provide ratings that reflect their agreement with one of two bi-polar statements at each end of the continuum (e.g. ‘Strongly disagree’ – ‘Strongly agree’) [110].

